### Procedure

Patients are randomly assigned to either one of the active conditions or the waiting-list control condition. The patients in the active conditions use the program either with individual or group-guided support. The waiting-list control group gets to use the program 12 weeks later. All three groups are assessed at baseline (t0), immediately after completing the program (t1; 12 weeks) and at follow-up six months after randomization (t2). Additionally, participants in both of the active conditions complete self-report measures of SAD (Social Phobia Scale & Social Interaction Anxiety Scale; [30]) every two weeks. Other process measures are included according to the treatment condition (Working Alliance Inventory [31] for the group with individual support; Group Questionnaire [32], for the group-guided condition).

### Measurements

For an overview of assessment at baseline, 12-week-posttreatment and 6-month follow-up see Table 2.

**Table 2 T2:** Measurements and time of assessment

**Instrument**	**Abbreviation**	**Aim**	**Time of assessment**
**Clinician administered**			
Structured Clinical Interview for DSM-IV Axis I Disorders	SCID-I	DSM-IV Axis I disorders	Pre, post (12 weeks), follow-up (6 moths)
**Self-report ratings**			
Primary Outcome Measures			
Social Phobia Scale	SPS	Symptoms of SAD	Pre, post, follow-up
Social Interaction Anxiety Scale	SIAS		
Secondary Outcome Measures			
Beck Depression Inventory	BDI-II	Symptoms of depression	Pre, post, follow-up
Brief Symptom Inventory	BSI	Psychiatric symptoms	Pre, post, follow-up
Inventory of Interpersonal Problems	IIP-64	Interpersonal difficulties	Pre, post, follow-up
SF-12 Health Survey (Quality of Life)	SF-12	Quality of Life	Pre, post, follow-up
Client Satisfaction Questionnaire	CSQ-8	Client satisfaction	Post
	ZUF-8		

### Primary outcome measures

#### Symptoms of SAD and diagnostic status

Social phobic symptoms and diagnostic status at post-treatment are the main outcome variables studied. Symptoms of SAD will be measured with self-report questionnaires using the Social Phobia Scale and the Social Interaction Anxiety Scale (SPS & SIAS; [30]). These two companion measures assess fears of being judged by others during daily activities (SPS) and more general fears in social interaction (SIAS), respectively. They have been found to be valid, reliable and useful for clinical and research purposes [33]. The patients’ diagnostic status will be assessed with a telephone interview conducted by trained raters and using the Structured Clinical Interview for DSM-IV (SKID-I [34]).

### Secondary outcome measures

#### Beck depression inventory II

To account for the high comorbidity of social phobia and depression, clients are asked to complete the German version of the Beck Depression Inventory II [35]. The BDI II is one of the most widely used self-report measures to assess depression in research in clinical practice. It consists of 21 items to be rated on a 4-point Likert-scale and has shown robust psychometric properties for internet delivery with SAD clients [15].

#### Brief symptom inventory

As a measurement of psychiatric symptoms, participants complete the German version of the Brief Symptom Inventory (BSI) [36]. The BSI assesses psychological distress on 9 dimensions such as anxiety, insecurity in social situations, depressiveness and compulsivity. The participants are asked to rate the occurrence of symptoms within the last week. Due to this restriction, the BSI is sensitive to change. As an economic screening instrument with robust psychometric properties, this inventory is commonly administered to detect pre-post changes [37].

#### Inventory of interpersonal problems

The Inventory of Interpersonal Problems (IIP) is used to identify sources of relational distress [38]. This self-report measure is designed to assess difficulties in interpersonal behavior on eight factor-analytically derived dimensions (domineering, vindictive, cold, socially avoidant, nonassertive, exploitable, overly nurturant, intrusive). The resulting T-scores of these subscales can be understood within the “interpersonal circumplex” model of personality [39]. The IIP has shown adequate psychometric properties [40].

#### Short-form health survey-12 (SF-12)

The SF-12 Health Survey is a condensed version of the Short Form Health Survey (SF-36) measuring physical and mental health on two subscales. Participants are asked to report the presence and severity of physical and mental problems over the course of the last 4 weeks. Its 12 items cover pain, psychological problems as well as impairments in everyday life. Because of its good re-test reliability and brevity, the SF-12 is widely used as an estimate of general quality of life [41].

#### Client satisfaction questionnaire (ZUF-8)

In order to learn more about the acceptance of web-based interventions, global client satisfaction is assessed at post-treatment using the Client Satisfaction Questionnaire (ZUF-8) [42]. The ZUF-8 is a translation of the Client Satisfaction Questionnaire [43] which was originally developed to measure satisfaction with inpatient treatment. We adapted the German version in this study to assess contentment with the web-based self-help treatment.

#### Adherence to treatment /completion rates

Adherence to treatment and completion rates as one of the major problems of internet-based self-help will be assessed, as well. More specifically, lessons completed, time spent in the self-help program and usage of the different types of support will be analyzed to identify potential mediating effects.

### Process measures

#### Change in social phobic symptoms

During the intervention, participants in the active conditions are asked to rate their symptoms of SAD every two weeks (SPS & SIAS).

#### Working alliance and group processes

Because the role of the therapeutic relationship within internet-based intervention has yet to be fully understood, patients in the condition with individual support fill out the Working Alliance Inventory (WAI [31]). This instrument comprises bond, goal and task aspects of the working alliance and shows an adequate reliability. Consistent with previous research on internet-based interventions, a modified version of the WAI is administered to account for the self-help character of the treatment [29].

Correspondingly, participants in the group guided self-help condition are asked to report their experiences with the Group Questionnaire (GQ-D [44]). The GQ-D assesses helpful aspects of relationships within small groups, hereby enabling us to further examine group processes in web-based interventions.

### Power and sample size calculation

The main endpoints in this study are the reduction of social phobic symptoms and the patients’ diagnostic status. Regarding differences between the two active conditions, we want to be able to demonstrate standardized effect sizes (Cohen’s d) of 0.35, since smaller effects are considered clinically insignificant. At an α error level of 0.05, a statistical power (1-Beta) of 0.80, and a correlation between pre- and post-measurements found in our previous studies, 60 participants are needed in each of the two active conditions. Based on earlier findings, we expect large differences in the comparison of the active conditions and the waiting-list control. Power analysis shows that a sample size of 30 in the waiting-list control group will be sufficient to show effect sizes of this magnitude.

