### Randomization

After checking the inclusion criteria, a weighted randomization procedure is used in which 60 participants are assigned to each of the active treatment conditions and 30 participants to the waiting-list control group. The allocation list is produced by a computerized random number generator operated by an independent researcher and is unknown to the investigators.

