### Analysis

Intent-to-treat samples will be used to analyze data. The choice of statistical approach depends on the amount of missing data at post- and follow-up-assessment. In the case of less than 12% missing data, the Last Observation Carried Forward (LOCF) method will be applied to estimate effects. Then, the primary outcome will be computed with an analysis of covariance (ANCOVA), using the pre-scores as a covariate and the post-scores as the dependent variable.

If more than 12% of participants stop the treatment, we will use linear mixed models. This method is recommended for intent-to-treat-analyses with a high amount of dropouts due to its potential to reduce bias caused by missing data. The level of significance will be 5% (α = 0.05). Significance testing of the diagnostic status and clinically significant change will be conducted with chi-square tests. Regression analyses will be used to identify predictors of treatment outcome.

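### For group versus individual support, the 80% power at 60 per arm applies to the symptom scores only; diagnostic status, also a main endpoint, has roughly 31–41% under mid-range assumptions

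*Protocol article*

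**What the plan says.** Two kinds of main outcome are declared. Under the primary outcome measures the protocol states "Social phobic symptoms and diagnostic status at post-treatment are the main outcome variables studied", and the section on power and sample size repeats it: "The main endpoints in this study are the reduction of social phobic symptoms and the patients’ diagnostic status".

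For the comparison of the two active arms, that section gives one target: "we want to be able to demonstrate standardized effect sizes (Cohen’s d) of 0.35, since smaller effects are considered clinically insignificant". The other inputs are "At an α error level of 0.05, a statistical power (1-Beta) of 0.80, and a correlation between pre- and post-measurements found in our previous studies", and the result is "60 participants are needed in each of the two active conditions". The value of the correlation is not given. No remission rate, difference in proportions or odds ratio appears anywhere in the document.

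The Analysis section treats the two outcomes differently. When little is missing, the scores are analysed by "analysis of covariance (ANCOVA), using the pre-scores as a covariate and the post-scores as the dependent variable". For diagnosis, "Significance testing of the diagnostic status and clinically significant change will be conducted with chi-square tests". The inclusion criteria require every participant to meet the diagnostic criteria for SAD in the telephone interview.

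**The concern.** The sample-size section names two main endpoints and then gives one sample size with one power, so a reader will take the 80% to cover both. It cannot. A pre-post correlation reduces the residual variance of a continuous score. Baseline diagnosis is the same for everyone, so it has no variance and predicts nothing, and the chi-square test takes no other baseline information. Reducing the outcome to a yes/no diagnosis also loses information.

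Group versus individual support is the trial's distinctive question. If an effect of the target size is real, the comparison of diagnoses would more likely than not be non-significant. It could then be read as contradicting a positive result on the scales, or as a negative finding from an adequately powered test.

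**Working it through.** **Inputs from the protocol:** d = 0.35, α = 0.05, power 0.80 and 60 per active arm (power section); chi-square for diagnosis (Analysis section). **Assumptions:** two-sided testing, complete data, comparator-arm remission of 30–60%, and an effect on diagnosis equivalent to d = 0.35.

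**1. The plan's own figure.** Without a covariate, n per arm = 2(1.96 + 0.8416)²/0.35² = 128.1, so 129, and 60 per arm gives 48% power. With ANCOVA the requirement is multiplied by (1 − r²). Setting 128.1(1 − r²) = 60 gives r = 0.73, at which power is 80.1%. A change-score analysis would need r = 0.766. The figure of 60 is therefore attainable for the scores, but only through a fairly high correlation, and it cannot be confirmed because r is not stated.

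**2. Converting d = 0.35 to remission proportions** (comparator p, other arm q):
- Logistic: odds ratio = exp(0.35π/√3) = 1.89.
- Probit (normal latent variable): q = Φ(z(p) + 0.35), where z(p) is the normal quantile.
- Cohen's h: 2·arcsin√q − 2·arcsin√p = 0.35.

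**3. Power of the chi-square test, n = 60 per arm.** With p̄ = (p + q)/2,

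power = Φ{[(q − p) − 1.96√(2p̄(1 − p̄)/n)] / √([p(1 − p) + q(1 − q)]/n)}.

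For p = 0.50 and q = 0.654 (logistic): (0.154 − 1.96 × 0.0902)/0.0891 ≈ −0.26, giving 0.40.

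| Comparator remission | Logistic: q, power, n per arm for 80% | Probit: q, power, n per arm for 80% | Cohen's h: q, power |
|---|---|---|---|
| 30% | 44.7%, 0.38, 169 | 43.1%, 0.32, 212 | 46.9%, 0.48 |
| 40% | 55.7%, 0.41, 158 | 53.8%, 0.33, 203 | 57.4%, 0.48 |
| 50% | 65.4%, 0.40, 162 | 63.7%, 0.33, 205 | 67.1%, 0.48 |
| 60% | 73.9%, 0.37, 179 | 72.7%, 0.31, 217 | 76.2%, 0.48 |

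Outside this range power is lower under the first two conversions: about 0.21–0.22 at 10% remission and 0.24 at 80%.

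**4. Difference detectable with 80% power at 60 per arm:** 30% v 55.1%, 40% v 65.3%, 50% v 74.6%, 60% v 82.9%. That is 22.9 to 25.3 percentage points.

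**5. Gain from baseline adjustment (simulation).** With a normal latent effect of 0.35, chi-square power of about 0.31–0.34 rises to about 0.35–0.39 if baseline severity correlates 0.5 with the latent outcome, and to about 0.46–0.47 at 0.7–0.73. Under the more favourable logistic conversion the corresponding rises are from 0.40 to 0.44 (correlation 0.5) and from 0.42 to 0.54 (0.7). None of these comes near 0.80.

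**The case against.** The strongest reply is that the size of the shortfall is built on assumptions. The protocol gives no remission rates, and translating d = 0.35 into an odds ratio supposes that diagnosis is a threshold on a latent variable shifted as much as the self-report scores. Diagnosis comes from a separate rater interview, and its effect could be larger or smaller. This stands as a limit on the figures. It does not rescue the power statement, because every conversion tried stays below 50% without adjustment, and the protocol offers no basis of its own for 80% on this endpoint.

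It is also fair that an unadjusted chi-square is valid in a randomised trial. Adjustment is a gain in precision, not the correction of an error, and the gain is modest.

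On scope, the objectives section predicts superiority of group over individual support for adherence, satisfaction and cost, and makes no explicit prediction of better remission. But the stated primary aim includes comparing the two formats on social anxiety symptoms, and the power section discusses this contrast directly after naming both endpoints. Nor does the protocol require success on both endpoints jointly; the problem is what the power statement implies, not a failed joint criterion.

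Three stronger readings are tempting and are not supported:
- **LOCF turns each missed interview into a continued diagnosis.** The LOCF sentence leads into the ANCOVA of pre- and post-scores. How missing interviews are handled is not stated, and an article may leave that to the full plan.
- **A linear mixed model would be fitted to a binary outcome.** The protocol assigns diagnosis its own test and never says this.
- **A random effect for support groups is needed here.** Nothing in this point depends on it.

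**Conclusion.** The point holds for group versus individual support. The 80% power at 60 per arm belongs to the symptom scores. For diagnostic status, with assumed comparator remission of 30–60% and an effect equivalent to d = 0.35, the planned test has about 31–41% power (logistic or probit conversion), or about 48% under Cohen's h. It reaches 80% only for differences of about 23–25 points. The exact figures rest on those assumptions, two-sided testing and complete data; dropout would lower them. The conclusion that power is far below 80% does not depend on which conversion is used.

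A reader might extend this to the waiting-list comparison or conclude that 60 per arm is wrong for the scales. Neither follows. The protocol expects large differences from the waiting list; an assumed latent d of 0.8–1.0 with 10–30% waiting-list remission gives about 63–95% power at 60 v 30. For the scales, 60 per arm is consistent with r of about 0.73.

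**What to change.** In the power and sample-size section, state that the 80% power for the two active arms applies to SPS and SIAS only. Add the difference in remission that 60 per arm can detect with 80% power (about 23–25 percentage points for comparator remission of 30–60%), with the remission rates assumed.

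In the Analysis section, replace the chi-square test for diagnostic status with logistic regression adjusted for baseline SPS and SIAS, and report a standardised risk difference with its confidence interval. Making diagnosis a secondary endpoint for this one contrast is optional.

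No extra participants or data are needed, since both baseline scores are already collected. The price is a less favourable power statement and slightly more analysis work. Adjusted power would still be only about 35–47% with the normal latent effect (up to about 54% with the logistic conversion), so the wording change matters more than the change of model.

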### Analysis

Intent-to-treat samples will be used to analyze data. The choice of statistical approach depends on the amount of missing data at post- and follow-up-assessment. In the case of less than 12% missing data, the Last Observation Carried Forward (LOCF) method will be applied to estimate effects. Then, the primary outcome will be computed with an analysis of covariance (ANCOVA), using the pre-scores as a covariate and the post-scores as the dependent variable.

If more than 12% of participants stop the treatment, we will use linear mixed models. This method is recommended for intent-to-treat-analyses with a high amount of dropouts due to its potential to reduce bias caused by missing data. The level of significance will be 5% (α = 0.05). Significance testing of the diagnostic status and clinically significant change will be conducted with chi-square tests. Regression analyses will be used to identify predictors of treatment outcome.

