### Objective and research questions

The primary aim of this study is to evaluate whether the newly developed group guided self-help treatment for SAD is effective in reducing social anxiety symptoms when compared to a waiting-list control group and an individually guided self-help treatment. It is expected that the active intervention groups will be superior to the waiting-list control group with regard to primary social anxiety measures and secondary outcomes such as depression, general symptomatology, interpersonal problems and quality of life. It is further expected that the group guided self-help treatment will be superior to the individually guided self-help treatment in terms of adherence to treatment, treatment satisfaction and cost as estimated from the amount of therapist time required for each client.

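### The 12% rule that selects the primary SPS/SIAS analysis has two non-matching triggers, and its LOCF branch biases the group-versus-individual contrast whenever missing post-scores differ by arm

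*Protocol article*

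**What the plan says.** The Analysis section of the protocol article begins with a general statement: "The choice of statistical approach depends on the amount of missing data at post- and follow-up-assessment". Two branches follow.

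- First branch: "In the case of less than 12% missing data, the Last Observation Carried Forward (LOCF) method will be applied to estimate effects". Here "the primary outcome will be computed with an analysis of covariance (ANCOVA), using the pre-scores as a covariate and the post-scores as the dependent variable".
- Second branch: "If more than 12% of participants stop the treatment, we will use linear mixed models". The reason given for this method is "due to its potential to reduce bias caused by missing data".

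Three other places bear on the point. Objective and research questions expects that "the group guided self-help treatment will be superior to the individually guided self-help treatment in terms of adherence to treatment". The section on adherence and completion rates measures adherence by sessions finished, time in the programme and use made of the support. Under Procedure, "participants in both of the active conditions complete self-report measures of SAD" at two-week intervals, besides the assessments that all three groups share. Power and sample size calculation sets d = 0.35 as the smallest difference of interest between the active arms, with 60 participants in each.

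**The concern.** There are two linked problems.

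First, the rule does not identify one analysis. The LOCF branch is triggered by missing assessments and the mixed-model branch by stopping treatment. A participant can leave the programme and still return the 12-week questionnaire, or finish it and not return the questionnaire. Where the two counts disagree, the choice of primary model is open at the time of analysis. The rule also counts missing data at follow-up, although the primary outcome is at post-treatment.

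Second, LOCF is not neutral between arms. If symptoms improve during treatment, a drop-out frozen at an earlier score looks worse than he or she would have been. The arm with more missing post-scores is penalised more. This affects the comparison of the two active arms, where the target effect is small enough for a modest artefact to matter.

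**Working it through.** **Step 1. Does the rule name exactly one analysis?** Set the two conditions against possible outcomes (illustrative percentages):

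| Missing assessments | Stopped treatment | LOCF-ANCOVA condition met? | Mixed-model condition met? |
|---|---|---|---|
| 8% | 25% | yes | yes |
| 15% | 8% | no | no |
| exactly 12% | exactly 12% | no | no |

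The denominator is not stated either. Twelve per cent is 0.12 × 150 = 18 participants overall, 0.12 × 120 = 14.4 across the active arms, or 0.12 × 60 = 7.2 in one active arm. Exactly 12% can occur only with the first, since the others are not whole numbers.

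**Step 2. Size of the LOCF bias.** Let D be the true improvement, equal in both active arms, in SD units. Let m_I and m_G be the missing fractions in the individual and group arms, and c the share of D already present in the score carried forward. With no true difference between the arms, and drop-outs who would have improved like the others,

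spurious difference = (m_I − m_G) × D × (1 − c).

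The protocol gives none of D, m_I, m_G or c, so all are assumptions. With c = 0 (baseline carried forward):

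| D (SD) | 15% vs 5% missing (pooled 10%) | 17% vs 5% missing (pooled 11%) |
|---|---|---|
| 0.5 | 0.10 × 0.5 = 0.050 | 0.12 × 0.5 = 0.060 |
| 0.8 | 0.080 | 0.096 |
| 1.0 | 0.100 | 0.120 |
| 1.2 | 0.120 | 0.12 × 1.2 = 0.144 |

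Against the 0.35 target: 0.050/0.35 = 14% and 0.144/0.35 = 41%. With c = 0.5 (two-weekly scores carried, half the change captured) the range is 0.025-0.072 SD, or 7-21% of the target. With m_I = m_G it is zero. With the missing rates reversed, the sign reverses.

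These splits reach the LOCF branch only if the 12% is pooled. If it applies to each arm, at most 7 of 60 may be missing in either arm. Then 7 against 3 missing gives (4/60) × 0.5 to (4/60) × 1.2 = 0.03-0.08 SD. The extreme of 7 against 0 gives (7/60) × 0.5 to (7/60) × 1.2 = 0.06-0.14 SD.

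**Step 3. Simulation check.** LOCF followed by ANCOVA was simulated with 60 per arm, baseline carried forward, no true difference and 4,000 replicates per scenario. The pre-post correlation was set at 0.73. The protocol gives no value, but this one approximately reproduces its sample size: n = 2(1.96 + 0.842)²(1 − 0.73²)/0.35² ≈ 60 per arm.

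- 15% vs 5% missing, D = 0.5, 0.8, 1.0, 1.2: mean spurious advantage 0.048, 0.082, 0.100, 0.120 SD; two-sided type I error 0.068, 0.099, 0.127, 0.132.
- 10% vs 10% missing: bias no larger than 0.002 SD; type I error 0.046-0.050.
- Missing rates reversed (5% individual, 15% group), D = 1.0: 0.10 SD against the group arm; type I error 0.122.

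The simulation agrees with the formula.

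**The case against.** The best defence is that the opening sentence of the rule names missing assessment data as the governing quantity, so the reference to stopping treatment may be loose wording for the same thing. That is a plausible reading, but the text does not settle it, and the article itself measures programme use separately from the outcome questionnaires. The ambiguity stands.

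It can also be said that the threshold limits the harm, that equal loss produces no bias, and that two-weekly scores bring the last observation closer to the endpoint. All of this is right. It limits the size but does not remove the problem. If drop-outs truly stay at their last score, LOCF is not wrong for them, but the article does not argue that they do.

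A reader might infer several stronger points, which the article does not support:

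- *That it predicts a bias towards the group arm.* It predicts better adherence, defined by programme use, and nowhere predicts fewer missing post-scores. The step from one to the other is reasonable but remains an inference.
- *That the method is chosen by looking at outcomes.* The rule depends on the amount of missing data, which can be counted without seeing scores or allocation.
- *That unequal measurement biases the comparison with the waiting list in the active arms' favour.* No direction can be shown. If the active arms lose more participants, LOCF would generally work against them.
- *That the mixed-model branch loses power.* This needs a particular treatment of baseline, which the article does not specify.

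**Conclusion.** The point holds in two parts. The mismatch of triggers is evident from the Analysis section and needs no assumption: both branches, or neither, can apply. The LOCF bias is conditional. It requires unequal missing post-scores, improving symptoms, and drop-outs who would have improved beyond the score carried forward. Under the assumed values it is about 0.05-0.14 SD with baseline carried forward, roughly half that if half the change is already captured, and nil with equal loss. It runs towards whichever arm has fewer missing post-scores; only if better adherence carries over to assessment retention is that the group arm.

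The section's own reason for mixed models applies equally below 12%, and nothing in the text justifies withholding them there. The point concerns SPS and SIAS only: diagnostic status, also primary, is tested by chi-square and is not affected by the switch between ANCOVA and mixed models.

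**What to change.** Delete LOCF and the 12% switch. Prespecify one likelihood-based linear mixed model, fitted to all observed scores, as the primary SPS/SIAS analysis whatever the missing rate. Adjust for baseline, either as a covariate or by constraining the baseline means to be equal across arms, and name the post-treatment contrast as the estimate. The model assumes that data are missing at random given the observed scores; the two-weekly scores make this more plausible for the group-versus-individual contrast. Keep ANCOVA on observed post-scores, without imputation, as a sensitivity analysis.

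The cost is a change of wording in the analysis section, with no new data and no change in conduct. The Trial status section reports 83 participants as of April 2014 against a target of 150, so the rule could be fixed before the final data exist.

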### Description of the interventions

a) Internet-based individually guided self-help without peer support:

The main component of the 12-week treatment is a self-help program, which has been successfully evaluated in previous studies [15,23,26,27]. The theoretical background of this program is based on Clark & Wells’ well-established cognitive-behavioral treatment model [28]. The program contains eight text-based sessions, including several exercises (such as attention training) and diaries (e.g. diaries to identify and challenge dysfunctional assumptions). Participants are asked to work trough one session per week, repeat the exercises and fill in the diaries. One session can be completed in approximately 60 minutes. Table 1 shows an overview of the content. While working with the program, the participants receive individual support by psychologists via an integrated email function of the platform. The psychologists contact the participants on a weekly basis in order to provide structure and reinforce program use. The patients can use the email function to contact the psychologists whenever they want to. Supervision of the supporting psychologists is provided by the study direction. This intervention does not include any possibility of group-guided support (e.g. in a discussion forum).

b) Internet-based group guided self-help treatment:

Participants in the second active condition use the same internet-based self-help program as described above. In contrast, they will not be supported individually, but within groups of six participants. All members of one group start the intervention at the same time and use an integrated, protected discussion forum to communicate with each other under the guidance of a psychologist. At the beginning, the group members and the supporting professional introduce themselves. The group members are encouraged to share their experiences, problems and questions with each other. The messages posted in the forum are accessible to every group member and the psychologist, as well. Analogous to the first treatment condition, the psychologists contact the group on a weekly basis. The psychologists’ short messages aim at providing the group with structure and motivation.

The participants are asked to choose a pseudonym instead of their real name for the digital communication, so as to protect their privacy. The supporting psychologists supervise adherence to this guideline and will delete real names.

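### If outcomes correlate within the discussion groups of six, the planned ANCOVA and chi-square tests understate the standard error of the group-guided contrasts, and type I error rises modestly above 5%

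*Protocol article*

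**What the plan says.** Under Description of the interventions, both active arms use the same self-help program. Of the group-guided participants the article says: "In contrast, they will not be supported individually, but within groups of six participants". Members of a group begin together and write to one another in a shared, protected forum under a psychologist's guidance. The individually guided arm has no forum or other peer contact.

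Under Analysis, when less than 12% of data are missing, values are carried forward and "the primary outcome will be computed with an analysis of covariance (ANCOVA), using the pre-scores as a covariate". The pre-score is the only covariate named. For the binary outcomes, "Significance testing of the diagnostic status and clinically significant change will be conducted with chi-square tests". Linear mixed models replace ANCOVA if more than 12% stop treatment. The reason given is bias from missing data, and discussion group is not mentioned.

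Under Power and sample size calculation, for the comparison of the two active arms, "we want to be able to demonstrate standardized effect sizes (Cohen’s d) of 0.35". The remaining inputs are "At an α error level of 0.05, a statistical power (1-Beta) of 0.80" and "a correlation between pre- and post-measurements found in our previous studies", from which "60 participants are needed in each of the two active conditions". Neither section mentions an ICC or a design effect.

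**The concern.** Six people who start together, read and answer each other's messages and share one psychologist's guidance may end up more alike than six people treated separately. The protocol relies on this: the Discussion expects group communication to bring mutual support, motivation and learning from one another, and Process measures includes a questionnaire on group processes. Because only one of the three arms is grouped, the design is partially nested.

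ANCOVA and the chi-square test, as named, take every participant as an independent unit. If outcomes within a discussion group are positively correlated, the mean (or proportion) in the group-guided arm is less precise than these tests assume. Intervals for that arm's contrasts are then too narrow and p-values too small. The Objective is to evaluate the group format against both comparators, so both contrasts that answer it are exposed, on symptom scores and on diagnostic status.

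**Working it through.** **Inputs from the protocol article.** 60, 60 and 30 participants (Participants; Randomization). Group size m = 6 (Study design; Description of the interventions). Alpha 0.05, power 0.80, d = 0.35 (Power and sample size calculation). Number of groups = 60/6 = 10, which is derived, not stated.

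**Assumed.** Two-sided testing. ICC of the baseline-adjusted outcome within discussion group from 0.02 to 0.15, with equal total variance in all arms. The pre-post correlation ρ has no stated value.

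**1. The stated 60 per arm.** Without a pre-post correlation, n = 2(1.960 + 0.842)²/0.35² ≈ 128.1, so 129 per arm. ANCOVA multiplies the 128.1 by (1 − ρ²). Setting 128.1(1 − ρ²) = 60 gives ρ ≈ 0.73. A change-score analysis, with multiplier 2(1 − ρ), needs ρ ≈ 0.77. The figure of 60 is therefore attainable but cannot be confirmed. At ρ ≈ 0.73 under ANCOVA it leaves no allowance for clustering.

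**2. Design effect, group-guided arm only.** DE = 1 + (6 − 1) × ICC.

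**3. True variance over assumed variance.**
- Group against individual (60 v 60): R = (DE + 1)/2.
- Group against waiting list (60 v 30): R = (DE/60 + 1/30)/(1/60 + 1/30) = (DE + 2)/3.

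**4. Actual two-sided type I error** = 2[1 − Φ(1.96/√R)]. Example at ICC 0.05, group against individual: DE = 1.25, R = 1.125, √R = 1.061, 1.96/1.061 = 1.848, giving 6.5%.

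**5. Power with a valid standard error**, if power is 80% under independence: Φ(2.802/√R − 1.960). Number needed per arm = 60 × R, rounded up.

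| ICC | DE | SE ratio √R, group v individual | Type I, group v individual | Type I, group v waiting list | Valid power, group v individual | n per arm for 80% |
|---|---|---|---|---|---|---|
| 0.02 | 1.10 | 1.025 | 5.6% | 5.4% | 78% | 63 |
| 0.05 | 1.25 | 1.061 | 6.5% | 6.0% | 75% | 68 |
| 0.10 | 1.50 | 1.118 | 8.0% | 7.0% | 71% | 75 |
| 0.15 | 1.75 | 1.173 | 9.5% | 8.0% | 67% | 83 |

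These use normal quantiles. With ten groups and small-sample degrees of freedom, real power is slightly lower.

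**6. Simulation check.** 20,000 trials per ICC, ten groups of six against 60 independent participants, no treatment effect. For ICC 0, 0.02, 0.05 and 0.10, the naive ANCOVA rejected in 4.9%, 5.8%, 6.3% and 7.9%. The naive chi-square test (50% base rate, ICC on the latent scale) rejected in 5.3%, 6.2%, 6.3% and 7.6%. At ICC 0 there is no meaningful inflation.

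**7. How well the trial can estimate the ICC.** With ten groups of six, the one-way ANOVA estimate is zero or negative with probability P[F(9, 50) < (1 − ICC)/(1 + 5 × ICC)]. This is about 46%, 35% and 21% at true ICC 0.02, 0.05 and 0.10.

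**The case against.** - **The ICC may be small.** The main component is a self-help program common to both active arms, contact is asynchronous and at a distance, and the psychologist's weekly messages are short. This stands. A reader might infer that type I error certainly exceeds 5%, but the documents give no ICC and so support only a conditional statement.
- **The error is two-sided.** Only half of the false rejections favour the group format: 2.8%, 3.2% and 4.0% at ICC 0.02, 0.05 and 0.10, against a nominal 2.5%. This stands, and it argues against calling the inflation gross.
- **The waiting-list contrast matters less.** The protocol expects large differences there, so a moderately narrow interval is unlikely to change that conclusion. This stands in part. The contrast between the active arms, which sets their sample size, carries most of the concern.
- **A mixed model is planned, and its random effects may be left to an analysis plan that is not shown.** It is fair not to fault the article for leaving those effects unlisted, and the article does not exclude a group level. But the branch depends on dropout and is justified by missing data alone. It leaves the ANCOVA branch as written and does not replace the chi-square tests.
- **Psychologists may also induce clustering in the individual arm.** This is possible. The article does not say how many participants each psychologist supports, so no size can be given, and a random intercept for discussion group would not separate group from psychologist effects.

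A reader might also infer that every comparison in the trial is compromised. It is not: neither individual guidance nor waiting list contains discussion groups, so that contrast is not affected by group clustering.

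**Conclusion.** The concern holds in conditional form. The article fixes tests that assume independence for an arm delivered in interacting groups, and its own rationale gives reason to expect some positive within-group correlation. If the ICC lies between 0.02 and 0.15, nominal 5% tests run at about 5.6% to 9.5% for group against individual guidance and 5.4% to 8.0% for group guidance against waiting list. If the ICC is zero, there is no inflation. The same correlation takes power for d = 0.35 below the stated 80%. That loss is already in the design, and the naive analysis only hides it. The figures rest on full groups of six, equal total variance across arms, two-sided testing and 80% power under independence. The analysis should be changed, but the size is modest and does not make the trial uninterpretable.

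**What to change.** **Analysis.** Whichever missing-data branch applies, analyse the group-guided contrasts on symptom scores with a partially nested model: baseline score as covariate, a random intercept for discussion group in the group-guided arm only, and Satterthwaite or Kenward-Roger degrees of freedom because there are only about ten groups. For diagnostic status and clinically significant change, replace the chi-square tests by a mixed logistic model or a cluster-robust analysis with small-sample correction. Report the ICC with its interval, since the point estimate will be imprecise and often at zero. Record which psychologist supports each participant, so that clustering by psychologist can at least be described.

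**Power and sample size calculation.** State the pre-post correlation used and an assumed ICC, and restate power for the comparison of the active arms (about 75% at ICC 0.05 and 71% at 0.10, slightly lower with small-sample degrees of freedom).

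**Cost.** No additional outcome data are needed, and under Trial status recruitment was still open at 83 of 150. The price is a standard error about 2.5% to 17% larger for group against individual guidance, over ICC 0.02 to 0.15, and a less favourable stated power. Restoring 80% would take 68 per active arm at ICC 0.05 or 75 at 0.10. If recruitment stays at 60, the lower power should be disclosed.
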